**Figure 4 F4:**
[figure not shown]
The defined Gruen zones of the periprosthetic side (LCU Hip system) and contralateral side.

### Secondary outcome measurements

2.6

Consecutive conventional radiographs remain play an irreplaceable role in assessing and evaluating periprosthetic bone remodeling. Therefore, standard radiographs will be taken at each follow-up time point, which would be analyzed and measured by computer software to compare with the initial appearance on the radiographs taken immediately postoperatively. The cortical thickness will be measured in all 7 Gruen zones, and changes will be calculated to reflect the periprosthetic bone formation and simulated adaptation.^[38,40]^ Fitness of the distal stem within the isthmus of the femur will be evaluated on the anteroposterior radiograph, and according to the contact between the prosthesis and the femur, which would be classified as good (space <1 mm), fair (space 1–2 mm), or poor (space >2 mm).^[41]^ Femoral stem alignment in frontal plane will be measured and classified as neutral (within 3°), varus or valgus. The progress of radiolucent line and reactive line around the cementless femoral stem in the respective zones will be tracked.^[38,41,42]^ Periosteal bone reactions will be simply classified into incomplete or complete pedestal sign. Femoral component's subsidence will be measured and identified according to D’Antonio method.^[42]^ Biologic fixation and stability of the cementless implant will be evaluated using Engh grading scale (Table 2).^[43]^ The severity of heterotopic bone formation around the stem at each interval will be graded according to Brooker's classification.^[44]^ Besides, postoperative clinical outcomes including Harris hip score, Western Ontario and McMaster Universities Osteoarthritis Index (WOMAC) score will also assessed for functional evaluation.

**Table 2 T2:**
[figure not shown]
Engh grading scale for the radiologic evaluation of cementless total hip arthroplasty.

### Sample size

2.7

The sample size was calculated based on the data obtained from our earlier cross-sectional study (http://www.chictr.org.cn, ChiCTR1800017750). We detected a mean difference in BMD of 0.1 g/cm^2^ with a standard deviation (SD) of 0.2 in patients received THA with the Ribbed stem. Based on these assumptions, setting an α error at 0.05 and the power level at 90%, additional compensate for possible dropout rate of 20%, a sample size of 50 patients in each group is required. We expect to recruit 100 patients within a period of 1 year based on our annual THA volume.

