### Primary outcome measurement

2.5

The primary outcome in the present study is periprosthetic BMD changes, which will be accurately measured by dual-energy X-ray absorptiometry (DXA). Although innovative techniques as bone microarchitecture analysis (BMA) and high-resolution peripheral quantitative computed tomography (HRpQCT) have been developed to provide not merely BMD, but also more detailed information about the bone microarchitectural properties, DXA remains the most widely used and most thoroughly studied bone density measurement technology in research as well as in clinical practice.^[35,36]^ As a sensitive technique for determining BMD, DXA may actually detect the minor changes of periprosthetic BMD after THA, and facilitate the evaluation of periprosthetic bone remodeling.^[22,37]^ We will use the metal removal analysis algorithms of the Hologic Discovery instrument (Hologic Inc, Waltham, MA) to measure the periprosthetic BMD in 7 conventional regions of interest (ROIs) based on Gruen zones, which is the most often used protocol in evaluation of bone remodeling after the implantation of conventional femoral stems.^[38,39]^ BMD in each Gruen zone will be measured 2 days postoperatively on both prosthetic side and contralateral side, which will be taken as baseline value for an exact longitudinal comparison. Index-ROIs of the Ribbed and LCU stems will be defined based on the 1st postoperative pattern, this reference allows us to minimize the inter-time point variability and assuring measurement precision (Figs. 3 and 4).

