### Statistical analysis

2.8

Frequencies and percentages will be estimated for qualitative data, and mean value ± SD will be calculated for quantitative data. To compare the periprosthetic BMD changes of Gruen zones between the Ribbed and LCU stems, statistical analysis will be performed using the Student *t* test for unmatched pairs to examine the significance of BMD changes of ROI 1–7, at each follow-up time point. And for further description of periprosthetic BMD changes, mean average BMD changes of ROI 1–7 will be presented as difference of both absolute and relative values (%) referred to the postoperative measurement. To minimize potential influential factors and better understanding the periprosthetic bone remodeling, we will also compare the periprosthetic BMD changes between the prosthetic side to the contralateral side by a paired *t* test for the Ribbed and LCU stems, respectively. For all analysis, a 2-tailed value of *P* < .05 is defined as statistically significant. Statistical analysis will be performed using the software SPSS version 22.0 (IBM Corporation, Armonk, NY).

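### The 90% power in section 2.7 rests on a difference and SD not shown to describe the Ribbed–LCU difference in BMD change, so it is unsupported for the primary outcome

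*Protocol article*

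**What the plan says.** Section 2.5 defines the outcome: "The primary outcome in the present study is periprosthetic BMD changes". BMD in each Gruen zone at day 2 after surgery, taken on both the operated and the contralateral side, is the baseline. Section 2.8 compares the changes between the Ribbed and LCU stems with an unpaired t test in ROI 1 to 7 at each follow-up visit, and "a 2-tailed value of *P* < .05 is defined as statistically significant". A separate paired t test compares the prosthetic with the contralateral side within each stem.

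Section 2.7 gives the planning basis: "The sample size was calculated based on the data obtained from our earlier cross-sectional study". The values are introduced with "We detected a mean difference in BMD of 0.1 g/cm^2", "with a standard deviation (SD) of 0.2 in patients received THA with the Ribbed stem". With α 0.05, power 90% and 20% dropout, the section arrives at 50 patients per group, 100 in all. It does not say which two quantities differ by 0.1, nor for which zone or time point.

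**The concern.** An unpaired t test of change needs two planning inputs: the between-group difference in change, and the SD of change within a group. Section 2.7 offers values that, as described, are neither.

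- **Difference.** It is reported in patients with one stem. No LCU figure is given, so nothing shows that 0.1 is a Ribbed–LCU contrast.
- **SD.** It comes from a study described as cross-sectional. The SD of change from day 2 depends on how closely day-2 and follow-up BMD agree within a patient. The article gives no such information.

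This is separate from the choice of formula. Putting the same 0.1 and 0.2 into the two-sample formula would change the number of patients but would still not give the power for the primary comparison. At stake is how the result is read: without a target difference and a supported SD, a non-significant comparison of the stems cannot be judged against what the study was able to detect.

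**Working it through.** **Inputs from the article.** Difference 0.1 g/cm², SD 0.2, α 0.05, power 90%, dropout 20%, 50 per group (section 2.7); two-sided, unpaired test (section 2.8). Evaluable per group after dropout: 50 × 0.8 = 40.

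**Step 1: can the stated 50 be reproduced?** (1.960 + 1.282)² = 10.507.

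- Two-sample formula, n per group = 2 × 10.507 × (0.2/0.1)² = 84.06, so 85. Allowing for dropout: 85/0.8 = 106.25, so 107; or 85 × 1.2 = 102. Neither is 50.
- One-sample or paired formula, n = 10.507 × (0.2/0.1)² = 42.03. Unrounded, 42.03 × 1.2 = 50.4. Rounded up first, 43 × 1.2 = 51.6, so 52; 43/0.8 = 53.75, so 54.

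Only the paired form comes near 50. This fits 0.1 and 0.2 being the mean and SD of a prosthetic-versus-contralateral difference, which a cross-sectional study could supply. It is an inference; the article does not say so.

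**Step 2: what the primary comparison needs.** For a two-sample t test (noncentral t, two-sided α 0.05, 40 per group), 90% power requires a standardised difference of 0.734. For a between-stem difference in change of 0.1 g/cm², the largest admissible SD of change is 0.1/0.734 = 0.136.

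**Step 3: sensitivity, illustration only.** The article gives no SD of change. One way to span a range is to assume that 0.2 is the between-patient SD at a single time, equal at both times, with correlation ρ between day-2 and follow-up BMD. Then SD of change = 0.2 × √(2(1 − ρ)). Both ρ and this reading of 0.2 are assumptions.

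| Assumed ρ | SD of change | Power for 0.1 g/cm², 40 per group | Difference detectable at 90% power (0.734 × unrounded SD) |
|---|---|---|---|
| 0.5 | 0.200 | 60% | 0.147 |
| 0.7 | 0.155 | 81% | 0.114 |
| 0.8 | 0.126 | 94% | 0.093 |
| 0.9 | 0.089 | above 99% | 0.066 |

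The last two columns follow from the SD of change alone and hold however that SD arises. The ρ column applies only under the single-time reading. If 0.2 is the SD of a side-to-side difference, the article says nothing about which row applies.

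**The case against.** Four points deserve weight.

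- **The inputs may be less remote than they look.** A reader might infer that a cross-sectional study scans each patient once and so offers no usable input under any formula. The article does not support that. Section 2.1 calls its own baseline phase cross-sectional, yet section 2.5 scans both hips at baseline. A side-to-side difference is therefore a plausible meaning of 0.1 and 0.2, and section 2.8 plans a prosthetic-versus-contralateral comparison. α and the dropout allowance are also usable. This stands: the values are not shown to be relevant, which is less than saying they are invalid.
- **No direction is shown.** A reader might infer that the study is underpowered. The article does not support that either. It gives no correlation, and section 2.5 fixes the ROIs on the first postoperative pattern to limit variability between visits, which works towards a smaller SD of change. At an SD of 0.126 or 0.089 the stated 90% would be exceeded. This also stands.
- **The sensitivity range depends on one reading of 0.2.** This stands for the link to ρ, but not for the 0.136 threshold, which needs no interpretation of 0.2.
- **Pilot data are often imperfect.** Section 2.7 calls the values assumptions, and the Discussion says that these two stems have not been compared before to the authors' knowledge. That excuses uncertainty about the values. It does not excuse stating 90% power without saying which quantity they describe.

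**Conclusion.** The point holds as a lack of support. The stated 90% power is not shown for the Ribbed–LCU comparison of BMD change, because neither 0.1 nor 0.2 is identified as a between-stem difference in change or an SD of change. True power could lie on either side of 90%. The claim would be met at 40 evaluable per group only if the between-stem difference in change is at least 0.1 g/cm² with an SD of change of about 0.136 or less, or some equivalent pair; the article supports neither condition. Over SDs of 0.20 down to 0.089, power for 0.1 g/cm² runs from 60% to above 99%. These figures assume the two-sample t test of section 2.8 for one zone and one visit, and exactly 20% loss. No corrected sample size can be derived from the article.

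**What to change.** Keep 100 patients and revise section 2.7 as follows.

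1. Define the planning quantity as the Ribbed–LCU difference in BMD change from day 2, for a named Gruen zone and visit. Section 2.8 tests seven zones at each visit, so no single SD exists until one is named.
2. State the target between-stem difference in change.
3. State what the 0.1 and 0.2 from the earlier study compare.
4. Replace the 90% claim with the two-sample power, or the detectable difference, at 40 evaluable per group over a range of SD of change labelled as assumed. The table above shows the form.
5. Optionally, update the SD once from the planned day-2 and follow-up scans, using the SD pooled within stems with stem means not disclosed. Ignoring stem labels would inflate it: with equal groups, a within-stem SD of 0.089 and a true difference of 0.1, it becomes √(0.089² + 0.1²/4) = 0.102. Note that a 6-month SD may not hold at later visits.

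The cost is a rewording and, if step 5 is taken, one SD estimate from scans already planned. No patients are added. The stated power may become less favourable.

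### On the stated inputs, 50 patients per group do not give 90% power for the between-stem t test, and section 2.7 does not say which comparison was sized

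*Protocol article*

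**What the plan says.** Section 2.7 (Sample size) says the calculation was "based on the data obtained from our earlier cross-sectional study". The inputs are given as: "We detected a mean difference in BMD of 0.1 g/cm^2^ with a standard deviation (SD) of 0.2 in patients received THA with the Ribbed stem". With α at 0.05, it then states: "power level at 90%, additional compensate for possible dropout rate of 20%, a sample size of 50 patients in each group is required". The total is 100 patients. The paragraph names no test, no formula, no sidedness and no method of allowing for dropout. It does not say whether the comparison being sized is between the stems or within one stem.

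Section 2.8 (Statistical analysis) compares BMD changes between the Ribbed and LCU stems first, by a Student t test "for unmatched pairs to examine the significance of BMD changes of ROI 1–7, at each follow-up time point". It then adds a paired t test of the prosthetic against the contralateral side within each stem group. Significance is two-sided throughout ("For all analysis, a 2-tailed value of" P below .05). The Abstract and Introduction give the direct comparison of the two stems as the aim, and section 2.5 makes periprosthetic BMD change the primary outcome.

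Section 2.2 allows a withdrawn participant to be replaced, but only if time permits.

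**The concern.** A standardised difference of 0.1/0.2 = 0.5 is moderate. At 90% power, a two-sample comparison of that size needs well over 50 evaluable patients per group even before dropout is considered, so 50 including a 20% dropout allowance looks too few for the test that serves the study's aim.

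The source of the inputs is a second problem. A figure "with a standard deviation (SD) of 0.2 in patients received THA with the Ribbed stem" describes one stem only. Nothing in section 2.7 shows that it is a Ribbed-versus-LCU difference, and a cross-sectional study does not by itself supply the SD of a longitudinal change.

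At stake is a stated property of the design. A reader who sees 90% power will treat a non-significant between-stem result as more informative than the stated inputs justify.

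**Working it through.** **Inputs.** Difference δ = 0.1 g/cm², SD σ = 0.2, α = 0.05, power 90%, dropout 20%, 50 per group (all section 2.7). Two-sided unmatched t test between stems, and paired t test within stem (section 2.8). Normal quantiles: 1.960 and 1.2816. If 20% of 50 are lost, 40 per group remain.

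**Step 1: can the plan's 50 be reproduced?** Two routes come close.

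- One-sample or paired formula: n = (1.960 + 1.2816)² × (0.2/0.1)² = 42.03. Multiplied by 1.2, this is 50.4.
- Two-sample formula: n per group = 2 × (1.960 + 1.2816)² × (0.2/0.1)² = 84.06. Multiplied by 1.2, this is 100.9. Read as a total instead of a per-group number, it gives about 50 per group.

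Both routes inflate by 1.2. To have n patients left after a 20% loss, one divides by 0.8. For the paired formula that gives 42.03/0.8 = 52.5, or 54 if 42.03 is first rounded up to 43. The document does not say which route was used, if either.

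**Step 2: what the between-stem test needs.** The normal approximation gives 84.06, so 85 per group. The t-based solution is 85.03, so 86 evaluable per group. Enrolled: 86/0.8 = 107.5, so 108 per group.

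Two more lenient readings also fail to give 50:

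| Variant (two-sample, t-based) | Evaluable per group | Enrolled per group at 20% dropout |
|---|---|---|
| Two-sided, 90% power (as planned) | 86 | 108 |
| One-sided, 90% power | 70 | 88 |
| Two-sided, 80% power | 64 | 80 |

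**Step 3: power of the stated design, with δ = 0.1 and σ = 0.2 taken as the between-stem values.**

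| Evaluable per group | Between-stem t test, two-sided | Paired t test within stem |
|---|---|---|
| 40 (20% lost, none replaced) | 59.8% | 86.9% |
| 50 (full retention) | 69.7% | 93.4% |

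**Step 4: what 40 per group can detect.** At 90% power and SD 0.2, the detectable between-stem difference is 0.147 g/cm². Alternatively, for a difference of 0.10 the SD would have to be about 0.136.

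**Step 5: sensitivity to what the 0.2 means.** The document gives no SD of change. Suppose 0.2 is the SD of BMD itself at one time point. The SD of change is then 0.2 × √(2(1 − r)), where r is the within-patient correlation between visits. The document does not give r, so it is an assumption here. For a difference of 0.10 and 40 per group:

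| Assumed r | SD of change | Between-stem power |
|---|---|---|
| 0.5 | 0.200 | 60% |
| 0.7 | 0.155 | 81% |
| 0.77 | 0.136 | 90% |
| 0.9 | 0.089 | over 99% |

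If 0.2 is instead the SD of a within-patient difference, which the wording also allows, this range does not arise.

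**The case against.** The strongest reply is that the real between-stem power is unknown. The 0.1 and 0.2 are not stated to be a between-stem difference or an SD of longitudinal change, so putting them into a between-stem test gives a conditional figure. This stands. A reader might infer that the study's true power is 60%; the documents do not support that, and step 5 shows how far the figure moves with the meaning of the SD. It does not rescue the 90%, because 0.1 and 0.2 are the only basis offered for that claim.

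Second, 60% assumes the full 20% loss with no replacement, while section 2.2 permits replacement if time allows. This also stands, so the fair statement is a range of 60% to 70% on the stated inputs. Full retention still falls well short of 90%.

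Third, section 2.7 may have been written for the paired within-stem test, in which case the shortfall is small: 87% with 40 completers, and 93% if all 50 are retained. The text does not exclude this. But section 2.8 brings in the paired test as an addition, and the study's aim is the stem comparison, so the main test would then have no sample-size basis at all.

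Fourth, it is tempting to say that the authors used a paired formula by mistake. The match with 42.03 × 1.2 is suggestive, but a two-sample number read as a total fits as well, so the cause cannot be stated as fact. Nor does the document say that a non-significant zone would be read as showing that the stems behave alike; that is a risk in interpretation, not something planned.

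**Conclusion.** The point holds in this form: section 2.7's inputs do not support 90% power with 50 per group for the between-stem t test in section 2.8. That test needs 86 evaluable per group, about 108 enrolled. If 0.1 and 0.2 are accepted as the between-stem difference and SD of BMD change, power is about 60% with 40 completers and about 70% with 50. The paired reading also misses the target after the planned dropout, at 87%.

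The shortfall against the stated inputs is firm, because it is arithmetic on the document's own numbers. The achieved power is conditional on two assumptions: that Ribbed-only cross-sectional figures carry over to a between-stem difference in change, and that retention lies between 40 and 50 per group. These figures are for a single test at 0.05, with no adjustment for multiple zones or visits. The stated power should be corrected.

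**What to change.** Keep 100 patients and restate section 2.7, naming the between-stem unmatched t test as the comparison. Suggested wording:

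*Assuming a between-stem difference in BMD change of 0.10 g/cm² with SD 0.2, the unmatched t test at two-sided 0.05 has about 60% power with 40 evaluable patients per stem and about 70% with 50. With 40 per stem, power is 90% for a difference of 0.147 g/cm². The values 0.10 and 0.2 are assumptions taken from cross-sectional data on Ribbed-stem patients only.*

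Report between-stem differences with 95% confidence intervals, so that a non-significant result shows which differences remain plausible.

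The cost is wording, with no additional patients. The downside is that the stated power becomes less favourable.

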### Statistical analysis

2.8

Frequencies and percentages will be estimated for qualitative data, and mean value ± SD will be calculated for quantitative data. To compare the periprosthetic BMD changes of Gruen zones between the Ribbed and LCU stems, statistical analysis will be performed using the Student *t* test for unmatched pairs to examine the significance of BMD changes of ROI 1–7, at each follow-up time point. And for further description of periprosthetic BMD changes, mean average BMD changes of ROI 1–7 will be presented as difference of both absolute and relative values (%) referred to the postoperative measurement. To minimize potential influential factors and better understanding the periprosthetic bone remodeling, we will also compare the periprosthetic BMD changes between the prosthetic side to the contralateral side by a paired *t* test for the Ribbed and LCU stems, respectively. For all analysis, a 2-tailed value of *P* < .05 is defined as statistically significant. Statistical analysis will be performed using the software SPSS version 22.0 (IBM Corporation, Armonk, NY).

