### Study design

2.1

This is a 5-year prospective longitudinal cohort study, which will be conducted in The First Affiliated Hospital of Chongqing Medical University. It will start recruiting patients in September 2018 and is being prepared now. The study will be executed in 2 phases. Phase I is a cross-sectional study, which will be conduct during hospitalization to obtain the baseline data; phase II comprises a cohort follow-up study at 6 months, 1, 2, 3, 4, and 5 years after THA. Participants will be followed for at least 5 years, or until death.

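### The primary outcome is tested between stems 42 times (7 zones at 6 visits), each at two-sided P < .05, with no primary zone, summary or visit named, so the 5% error rate in the sample size does not apply to the study's claim

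*Protocol article*

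**What the plan says.** All references are to the protocol article.

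- **Outcome (section 2.5).** "The primary outcome in the present study is periprosthetic BMD changes". The instrument is used "to measure the periprosthetic BMD in 7 conventional regions of interest (ROIs) based on Gruen zones", and the 2-day postoperative scan is the baseline. No zone is singled out.
- **Visits (section 2.1).** "phase II comprises a cohort follow-up study at 6 months, 1, 2, 3, 4, and 5 years after THA". None of the six is singled out.
- **Between-stem test (section 2.8).** An unpaired Student t test is used "to examine the significance of BMD changes of ROI 1–7, at each follow-up time point".
- **Threshold (section 2.8).** "For all analysis, a 2-tailed value of *P* < .05 is defined as statistically significant". No adjustment, testing order or global test is given.
- **Summary measure (section 2.8).** A mean change over ROI 1–7, absolute and relative, is mentioned, but only as further description.
- **Side-to-side test (section 2.8).** Prosthetic and contralateral sides are compared by paired t test within each stem. That sentence names no zones or visits.
- **Sample size (section 2.7).** One difference (0.1 g/cm², SD 0.2), one alpha (0.05), 90% power and 20% dropout, giving 50 per group. No zone or visit is attached to these figures.

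**The concern.** A primary outcome needs a rule that says which result answers the question. Here 42 results have equal standing, and each may be called significant on its own. A significant difference in any zone at any visit could be reported as the primary finding, and nothing in the text says how to read, for example, two significant results out of 42.

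The sample size section assumes a single test with a 5% false-positive risk. The analysis section permits 42 chances. The error rate behind the 50 per group is therefore not the error rate of the claim that the stems remodel bone differently.

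**Working it through.** **The plan's own figures.** The plan states no study-wide error rate to reproduce, only the per-test 0.05. Its sample size does not reproduce for the planned unpaired test: 2 × (1.960 + 1.282)² × (0.2/0.1)² gives 85 per group after rounding up, or 85/0.8 = 107 with dropout, against the stated 50. A one-sample or paired formula gives 42.03, and 42.03 × 1.2 = 50.4, which is close to 50. That is a separate matter, but it bears on the power figures below.

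**Step 1: number of tests.** 7 zones (section 2.5) × 6 visits (section 2.1) = 42 between-stem tests. The 2-day scan is the baseline, so it adds none.

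**Step 2: expected false positives if the stems do not differ.** 42 × 0.05 = 2.1. This holds under any correlation.

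**Step 3: chance of at least one, if the tests were independent.** 1 − 0.95^42 = 1 − 0.116 = 0.884.

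**Step 4: allowing for correlation.** The tests are not independent. All six changes in a zone subtract the same baseline scan. With equal variances and a common correlation ρ between scans, each change has variance 2σ²(1 − ρ) and two changes have covariance σ²(1 − ρ), so they correlate at 0.5 whatever ρ is. The zones also come from one femur. The documents give no correlations, so those below are assumptions, exchangeable between zones and between visits. The values are simulated under no stem difference.

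| Zone r | Visit r | P(at least one P < .05) |
|---|---|---|
| 0.2 | 0.5 | 0.78 |
| 0.3 | 0.5 | 0.76 |
| 0.3 | 0.8 | 0.60 |
| 0.5 | 0.7 | 0.59 |
| 0.5 | 0.8 | 0.53 |
| 0.5 | 0.9 | 0.43 |
| 0.7 | 0.8 | 0.42 |
| 0.7 | 0.9 | 0.34 |
| 0.9 | 0.95 | 0.19 |

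Against the nominal 0.05, these run from 0.19/0.05 = 3.8 times to 0.78/0.05 = 15.6 times.

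**Step 5: what each remedy leaves in power.** Inputs are 0.1 g/cm² and SD 0.2 from section 2.7, with 50 × 0.8 = 40 completers per group.

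- One contrast at 0.05: 0.1/(0.2 × √(2/40)) = 2.236, and 2.236 − 1.960 = 0.276, so power is about 61% (60% with the t distribution).
- Bonferroni over 7 zones at one visit (0.05/7 = 0.0071): about 32%. Without adjustment, the seven-zone error rate would be 1 − 0.95^7 = 0.30 if independent.
- Bonferroni over all 42 (0.05/42 = 0.0012): about 16% by the normal approximation (14% with the t distribution). Holding 90% power would need 164 evaluable, or 164/0.8 = 205 enrolled, per group.

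**The case against.** **This is an observational cohort reported under STROBE, and zone-by-zone BMD description is informative.** That is fair, and labelling the tests exploratory would be an honest alternative. But the article declares a primary outcome, a powered sample size and a significance threshold, and its Discussion expects the findings to guide implant design. Those are not the terms of a purely descriptive study.

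**A separate analysis plan may deal with multiplicity.** This is weak here. The article itself fixes the test, zones, visits and threshold, and applies the threshold to every analysis. A later plan with a hierarchy or adjustment would have to change that rule, not merely add to it.

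**A false stem difference is likely, at 88%.** A reader might infer this from 42 tests, but the documents do not support it as a general statement. The figure assumes independence, which the shared baseline scan rules out. The chance is below one half at several of the correlations above.

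**There are 126 tests, counting 84 paired ones.** A reader might infer this too. The paired comparison would add 7 × 6 × 2 = 84 only if run for each zone, visit and stem, which the text does not say. Those tests are within-stem and do not enter the between-stem error rate.

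**The question lies in the proximal zones, so ROIs 1 and 7 should decide it.** No section says so. The aim is remodeling in general, and section 2.5 treats all seven zones alike.

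**Conclusion.** The point holds. Sections 2.1, 2.5 and 2.8 together fix 42 unadjusted between-stem tests of the primary outcome with no deciding contrast, while section 2.7 assumes one test. This is a stated rule, not a missing detail.

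With no stem difference, 2.1 false positives are expected. The chance of at least one is several times the nominal 5%: about 20% to 78% over the assumed correlations, with 88% as the independence reference. The count and the 2.1 rest on the text alone. The range rests on correlations that the documents do not supply, so the size of the inflation is uncertain, though even the most favourable case shown is nearly four times nominal. Whether a false finding is more likely than not cannot be settled from the documents.

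**What to change.** Before data are seen, name one primary between-stem contrast at one visit in sections 2.5 and 2.8, tested at two-sided 0.05. The candidate nearest the existing text is the mean BMD change over ROI 1–7 that section 2.8 already mentions, with its definition as an average across zones made explicit. Another zone or summary would serve equally if the investigators justify it. At that visit, report the seven individual zones with Holm adjustment or label them exploratory. Report the other visits as estimates with 95% confidence intervals and no significance claims. State the zones and visits, if any, to which the paired side-to-side test applies, and its status.

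The cost is a change of wording and a registry update. The downside is that fewer zone and visit results can be called significant.

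Naming one contrast restores the 5% error rate but not the stated 90% power, which on section 2.7's inputs is about 60% with 40 completers per group. Those inputs are not tied to any zone or visit, so the sample size should be restated with a difference and SD for the contrast chosen.

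### Visit-by-visit t tests drop the earlier scans of patients who leave, so late stem contrasts are biased if dropout depends on BMD differently by stem; one repeated-measures model per ROI would guard against this

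*Protocol article*

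**What the plan says.** The Study design section states: "This is a 5-year prospective longitudinal cohort study". Follow-ups are at 6 months and at 1, 2, 3, 4 and 5 years, six in all.

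For the primary outcome, periprosthetic BMD change, the Statistical analysis section sets an unpaired Student t test "to examine the significance of BMD changes of ROI 1–7, at each follow-up time point". Seven regions at six visits make 42 between-stem tests. Changes are reported as a "difference of both absolute and relative values (%) referred to the postoperative measurement", so each patient contributes one change value per region to each test. A second analysis will "compare the periprosthetic BMD changes between the prosthetic side to the contralateral side by a paired" t test within each stem group.

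The Sample size section allows for a "possible dropout rate of 20" per cent. The eligibility section says that patients who withdraw are discontinued and, time permitting, replaced.

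The article itself states the between-stem method. The point therefore concerns a stated choice, not a detail left to an unseen analysis plan.

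**The concern.** A t test at year 5 can use only patients scanned at year 5. A patient who leaves after year 3 contributes nothing to the year-4 and year-5 comparisons, although four earlier follow-up scans are on file and are probably informative about the missing ones. The analysed patients also change from visit to visit, so the series of results mixes bone remodeling with changes in who is measured.

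Loss related to BMD is plausible on the article's own reasoning. The Introduction ties aseptic loosening to bone resorption around the implant and names it the main cause of implant failure, and a revised stem is unlikely to yield another comparable scan. If the stems differ in resorption, which is the study question, such loss could differ by stem. The late visits, which are the reason for following patients for 5 years, are the most exposed.

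The plan also has no formal test of whether the course over time differs between stems.

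**Working it through.** **Inputs from the article.** 50 patients per group; difference 0.1 g/cm²; SD 0.2; two-sided α 0.05; power 90%; dropout 20%; six follow-ups.

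**Assumptions, not in the article.** Between-visit correlation of BMD change: exchangeable 0.5 or 0.8, or autoregressive 0.7 or 0.9. Loss: completely random, or driven by the patient's last observed change.

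**1. The plan's own figure.** The inputs are "We detected a mean difference in BMD of 0.1 g/cm^2^ with a standard deviation (SD) of 0.2" and "setting an α error at 0.05 and the power level at 90" per cent.
- One-sample (paired) formula: ((1.960 + 1.282) × 0.2 / 0.1)² = 42.03. Times 1.2 gives 50.4, close to the stated 50.
- The between-stem test needs twice that: 2 × 42.03 = 84.06, so 85 per group, or 85 / 0.8 = 106.25, so 107 with 20% dropout.
- This mismatch is a separate matter. It matters here because the comparison starts with about 70% power at 50 per group and about 60% at 40.

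**2. Full attendance.** SE = √(2 × 0.2² / 50) = 0.040. In simulation (50 per group, six visits, true difference 0.1, 2,000 runs per setting) the t test and the unstructured repeated-measures estimate agreed to rounding error.

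**3. 20% completely random loss.** Neither method is biased. The t-test SE is √(2 × 0.2² / 40) = 0.0447.
- Best case for the model, with every lost patient scanned at year 4: effective n = 40 / (1 − 0.2ρ²), which is 44.3, 45.9 and 47.7 for ρ = 0.7, 0.8 and 0.9. The SE falls by 1 − √(40/44.3) = 5% to 1 − √(40/47.7) = 8%.
- Loss spread over the visits: effective n about 41 to 46, so the SE falls by 1 − √(40/41) = 1% to 1 − √(40/46) = 7%.
- Simulated SE: 0.044–0.045 for the t test, 0.042–0.044 for the model. Power: about 60–61% against 63–67%. Over all random-loss settings examined, the gain in SE was at most about 10%.

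**4. Loss driven by earlier BMD change, 20% overall.** Year-5 stem contrast:

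| Mechanism | t-test bias (g/cm²) | Model bias | Model SE relative to t test |
|---|---|---|---|
| One group only | about 0.02 to 0.04 | about 0 | 2–6% smaller |
| Opposite directions in the two groups | 0.041 to 0.062 | about 0 | about equal (0.99–1.01) |
| Shared, no true difference | about 0 | about 0 | little or no gain |
| Shared, true difference 0.1 | from about 0 to an attenuation of 0.004–0.013; about 0.02 if dependence is strong | within 0.002 | little or no gain |

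The SE ratios in the first two rows come from the simulation in step 2. In some shared-mechanism settings the model's SE was 1–2% larger.

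**5. Hand check of the one-group figure.** Suppose the lowest 20% on year-4 change all leave one group. The mean of those who stay rises at year 4 by 0.2 × 0.280 / 0.80 = 0.070, where 0.280 is the normal density at the 20% point. With ρ = 0.8 the year-5 mean shifts by 0.8 × 0.070 = 0.056. That is the ceiling for loss decided at year 4 alone. The simulated 0.02 to 0.04 lies below it, as it should when loss depends only partly on BMD.

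**The case against.** The strongest reply is that nothing is wrong with any single t test. Each one compares one change value per patient, already referred to that patient's own postoperative scan. Leaving the correlation between follow-up visits unused does not invalidate it. That stands: the cost is unused information and exposure to selective loss.

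A reader might infer more than the article supports, in four ways.
- **That the late results are biased.** Bias in the contrast needs loss that depends on BMD differently by stem, or a shared mechanism together with a real stem difference. The article shows neither, and it gives 20% as a possible rate.
- **That the t test is unbiased only if loss is unrelated to BMD.** This is false for the contrast: with no true difference and the same mechanism in both groups, the two means shift equally.
- **That a mixed model is always more precise.** With full attendance it changes nothing at a given visit, and under BMD-related loss the gain can be nil. Effective sizes of 44 to 48 are a best case.
- **That it settles the attrition question.** It relies on missing at random. Loss that depends on BMD after the last scan, such as rapid resorption leading to revision between visits, is not covered.

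A further objection concerns baseline adjustment and also stands. Stems are not randomised, and the baseline is scanned 2 days after implantation in regions defined for each stem. Adding baseline BMD can therefore target a different contrast from the planned comparison of changes. It is also fair that the stated aim does not require a stem × visit test; this is a useful addition, not the repair of a contradiction.

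**Conclusion.** The point holds as a worthwhile improvement to a stated method, not as an error that invalidates the analysis. With the allowed-for 20% dropout, the planned tests ignore scans already collected and leave the late contrasts open to selective loss. If that loss depends on earlier BMD change in one group only, the year-5 bias is about 0.02 to 0.04 g/cm², or 20 to 40% of the planned 0.1; opposite mechanisms would give more. A shared mechanism gives mild attenuation at most, and only if the stems truly differ. Under purely random loss there is no bias, and the gain is an SE about 0 to 10% smaller. All these sizes rest on assumed correlations and dropout mechanisms; the article supplies only the SD, the difference, the group size, the visits and the dropout allowance.

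**What to change.** For each region, replace the visit-by-visit t tests with one linear mixed model for repeated measures. The outcome is change from the postoperative scan; the fixed effects are stem, visit and stem × visit; the covariance across visits is unstructured. Include every patient with a baseline and at least one follow-up scan. Read the stem contrast at each visit, with its confidence interval, and a stem × visit test from this model. Keep baseline-adjusted versions as a sensitivity analysis. State the missing-at-random assumption and report the reasons for loss by stem, so that readers can judge it.

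The cost is a change of wording and slightly more analysis work, with no new data; the stated SPSS version can fit the model. The wording should be fixed before outcome data are analysed. The change leaves four matters to be dealt with separately: loss that is not at random, confounding by non-random stem choice, the 42 between-stem tests, and a sample size that matches a one-sample calculation.
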